### Plans to give access to the full protocol, participant-level data, and statistical code {31c}

The full protocol is uploaded and publicly available on the project homepage (https://herzzentrum.umg.eu/precovery/). All plans for granting access to the participant-level dataset, participant dataset, and statistical code are regulated in the project’s internal publication rules. All the principle investigators have been informed accordingly.

#### Lead investigators

In each participating recruiting center, a lead investigator (senior physician with expertise in cardiology or heart surgery) is responsible for the adherence to study protocol, including identification, recruitment, data collection, and completion of CRFs at several time points. The lead investigator is responsible for training personnel in the recruiting center and communicating with the PRECOVERY coordinating center and the personnel of the prehabilitation center.

In each participating prehabiliation center, a lead investigator (senior physician with expertise in cardiac rehabilitation) is responsible for the adherence to study protocol, including training all involved prehabilitation personnel to provide the intervention “Karl-Heinz” according to the intervention manual. The lead investigator is responsible for the communication with the PRECOVERY coordinating center and the unblinded physicians in the recruiting center.

#### General assembly

The General Assembly is made up of the lead investigators from the recruiting and prehabilitation centers. In addition, the consortium leader, head statistician, and the representatives of additional project partners, such as AOK Health Insurance (AOK Lower Saxony), the Department of Health Economics and Health Services Research, University Medical Center Hamburg-Eppendorf (economic evaluation), Department of General Practice of the University Medical Center Goettingen (process evaluation), and the Department of Psychosomatic Medicine and Psychotherapy (intervention training concept). The General Assembly meets once quarterly to discuss the progress of the study, current challenges, and any changes to the protocol deemed necessary by the Steering Committee.

### Steering committee

One investigator from a recruiting center and one investigator from a prehabilitation center are voted to the Steering Committee, joining the consortium leader, a representative of the AOK Health Insurance (AOK Lower Saxony) and the head statistician. The Steering Committee is responsible for regularly (at least once per quarter) reviewing the progress of the study and, if required, making changes to the protocol to ensure the smooth running of the study.

#### Monitoring

The Clinical Trials Unit of the University Medical Center Goettingen provides the personnel and know-how for the monitoring of the PRECOVERY randomized controlled trial and ensures data integrity.

### Composition of the data safety management board, its role and reporting structure {21a}

The DSMB is made up of four renowned experts in the field and a member of the German Heart Foundation (Deutsche Herzstiftung) as patient representative. The DSMB meets quarterly via online video meeting with the consortium leader during the patient recruitment phase of the PRECOVERY project to review AEs and SAEs reported in the follow-up time points after the “Karl-Heinz” intervention. The DSMB will assess the trial progress and safety, and accumulated trial data will be reported to the DSMB by the study statistician. The four experts in the DSMB receive a small expense allowance for their participation in the activities of the PRECOVERY DSMB—the German Heart Foundation does not receive any expense allowance. At their discretion, the DSMC may also formulate recommendations relating to the selection/recruitment of participants, their management, improving adherence to protocol-specified regimens and matter relating to patient retention, and procedures for data management and quality control.

### Adverse event reporting and harms {22}

A selection of AEs and SAEs will be recorded to monitor certain safety aspects of the study intervention. After randomization, all adverse cardiovascular events, revascularization procedures, or other invasive cardiac interventions and all SAEs (cardiac and non-cardiac reasons) will be documented in the eCRF. As mentioned above, the DSMB will assess the trial progress and safety, making appropriate recommendations for discontinuation or modifications of the study as needed.

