**Exclusion criteria**
Lack of capacity to consent
Katz index 0
Need for treatment in an acute care hospital
Severe dementia or severe mental disorders, acute delirium
Diagnosis of acute alcohol or drug abuse
Unstable angina pectoris
Heart failure, NYHA IV
Myocarditis, hypertrophic obstructive cardiomyopathy, main stem stenosis ≥ 80%
Severe refractory cardiac arrhythmias
Recent aortic dissection
Peripheral arterial occlusive disease stage ≥ III according to Fontaine
Symptomatic carotid stenosis or carotid stenosis requiring therapy
Renal insufficiency requiring dialysis
Hepatic insufficiency, child B and child C
Advanced (metastasized) oncological disease
Neurological, orthopedic or rheumatic comorbidities that militate against physical training
Participation in another intervention study (participation in registry studies is allowed)

*Abbreviations *
*OPS* operation and procedure codes, *NYHA* New York Heart Association

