### Criteria for discontinuing or modifying allocated interventions {11b}

During the prehabilitation intervention, the supervising study physicians of the prehabilitation center will obtain feedback on the participants’ treatment experience minimum twice weekly during medical rounds. Therefore, the multimodal prehabilitation intervention can be adjusted at any time if necessary.

Adverse events (AEs) including serious adverse events (SAEs) will be documented in the medical record and transmitted to the recruiting center prior to the cardiac procedure. The cardiovascular AEs in form of major cardiac events (MACE) and predefined SAEs will be documented into the secuTrial® electronic database from the medical record after the prehabilitation intervention. To ensure blinding of study assessors, a non-blinded study investigator will fill cardiovascular AEs and SAEs of patients in the SMC and intervention group into the secuTrial® database at t2. An independent Data Safety Monitoring Board (DSMB) including national and international experts on cardiology, cardiac surgery, geriatrics, cardiac rehabilitation, prehabilitation, and patient advocates has been established. The DSMB reviews the cardiovascular AEs and SAEs of the prehabilitation intervention and SMC before the cardiac procedures on a quarterly basis and determines whether the safety of the patients is still ensured and whether the continuation of the study without any changes is justifiable, or—if necessary—makes recommendations for discontinuation or modifications of the study. To fulfill this task, the DSMB receives information about protocol deviations, the status of patient recruitment and the observed cardiovascular AEs and predefined SAEs.

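### Non-serious falls and training injuries during prehabilitation are neither entered in the eCRF nor listed for the DSMB, so they cannot be compared between arms

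*Protocol article*

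**What the plan says.** Section {22} of the protocol article, on adverse event reporting, says openly that capture is partial: "A selection of AEs and SAEs will be recorded to monitor certain safety aspects of the study intervention". It then gives the rule that applies from randomization onward: "all adverse cardiovascular events, revascularization procedures, or other invasive cardiac interventions and all SAEs (cardiac and non-cardiac reasons) will be documented in the eCRF".

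Section {11b}, on discontinuing or modifying the intervention, describes two levels of recording during prehabilitation. AEs of any kind "will be documented in the medical record and transmitted to the recruiting center prior to the cardiac procedure". Only part of them goes further: "The cardiovascular AEs in form of major cardiac events (MACE) and predefined SAEs will be documented into the secuTrial® electronic database". A non-blinded investigator makes the corresponding entry for both arms at t2. The DSMB is asked to determine "whether the safety of the patients is still ensured", and for this it receives "information about protocol deviations, the status of patient recruitment and the observed cardiovascular AEs and predefined SAEs". The interim analysis section {21b} repeats that list, without the word predefined.

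Table 3 sets a minimum of one active exercise unit of 30 minutes a day, five times a week, covering endurance, strength/flexibility and coordination. Participants are 75 or older. Table 2 excludes patients with "Neurological, orthopedic or rheumatic comorbidities that militate against physical training".

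**The concern.** The capture rule covers cardiac and serious events, whereas the intervention is supervised daily physical training in old patients. Falls and musculoskeletal injuries are foreseeable with such a programme, and the exclusion just quoted shows that the authors considered non-cardiac limits to training. Yet neither falls nor training injuries are named among the AEs to be recorded, in the outcomes section {12}, or in the assessment schedule (Table 4).

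Two things are at stake. The DSMB has to weigh prehabilitation against standard care before the procedure without this class of event in its listing. In addition, the Discussion presents the programme as a candidate for adoption into German routine care. If the final report shows no excess of minor training harm, readers will not be able to tell whether there was none or whether it was never tabulated.

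**Working it through.** No figure in the plan bears on this point, so the check sets the sections side by side and follows one event, a non-serious fall during a training session, through them.

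1. **Medical record ({11b}).** The fall is written down and sent to the recruiting center.
2. **eCRF ({11b} and {22}).** Under {22} the fall would have to be a cardiovascular event, a revascularization or other invasive cardiac intervention, or an SAE. Under {11b} it would have to be a MACE or a predefined SAE. It is none of these and is not entered under either section.
3. **DSMB ({11b} and {21b}).** The safety data listed are cardiovascular AEs and SAEs (predefined SAEs in {11b}). The fall is not among them.
4. **Outcomes ({12} and Table 4).** An AE/SAE item appears as a further endpoint and as a row from t2 to t6. Neither entry widens the selection that {22} defines. The complications in Table 4 and in {18a} relate to the cardiac procedure.
5. **Monitoring ({23}).** The monitor reads prehabilitation records sent to the recruiting centers. No database entry or DSMB report is said to follow.
6. **Control arm.** These patients stay at home until the procedure (Background {6a}). No matching record is described for them, so extracting the prehabilitation records later would give a count for one arm only.

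The same comparison shows that two sections disagree on what is captured:

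| | {11b} | {22} |
|---|---|---|
| Cardiovascular AEs | in the form of MACE | all |
| SAEs | predefined | all, cardiac and non-cardiac |

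A serious non-cardiac fall is therefore certain to be captured under {22}, but under {11b} only if it is on the predefined list.

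**Exposure, from the document.** The minimum is 5 active units a week × 2 weeks = 10 units per patient. With 211 intervention patients that is 211 × 10 = 2,110 units, or 2,110 × 0.5 h = 1,055 hours of training.

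**Illustrative size.** All event rates here are assumptions; the document gives none.

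- Patients affected: 211 × 0.05 = 10.6 and 211 × 0.10 = 21.1, so about 11 to 21.
- Power if such events were recorded, with 211 per arm and two-sided 5%: h = 2[arcsin(√p₁) − arcsin(√p₂)], and power = Φ(h·√(211/2) − 1.96).
- 10% versus 3%: h = 0.295; 0.295 × 10.27 = 3.03; power = Φ(1.07) = 0.86.
- 8% versus 3%: h = 0.225; 0.225 × 10.27 = 2.31; power = Φ(0.35) = 0.64.

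These figures show only that 422 patients could inform such a comparison at the chosen rates. The finding does not depend on them.

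**The case against.** The strongest reply is that this is a disclosed, risk-based choice. Section {22} says that a selection is recorded. The programme lasts two weeks and uses elements that the authors describe as not new. Much of the exclusion list is cardiovascular, which suggests where the main risk was thought to lie, and those events are captured. Physicians obtain patient feedback at least twice a week and can adjust the programme, so minor events can be noticed and acted on. This stands as far as care of the individual patient goes. It does not supply a count by arm.

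A second reply is that the generic mention of AEs and SAEs in {12}, in Table 4 and in the DSMB section {21a} may mean wider capture, or that the full protocol lists falls among the predefined events. The generic wording cannot override an explicit list. The full protocol is not shown and could add fields, but the rule as the article states it would then need correcting.

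A third reply concerns the remedy. Intervention patients are observed all day by staff, controls rely on memory at home, and the question would be asked unblinded. Minor events would tend to be over-counted in the intervention arm. This is right. An identical question reduces the bias but does not remove it.

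A reader might go further and infer that such events never reach anyone, or that falls are the harm most likely to result from the training. The document supports neither reading. The events do reach the medical record, the recruiting center and potentially the monitor, and nothing in the text ranks the likely harms or gives a rate.

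**Conclusion.** The point holds in a limited form. As written, non-serious falls and training injuries are documented locally, but they are not in the eCRF and not among the data listed for the DSMB. The trial therefore cannot compare this foreseeable harm between arms. Serious falls and injuries are captured under {22}, although the narrower wording of {11b} makes that less clear than it should be. It would be wrong to conclude that non-cardiac safety goes unmonitored.

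The size cannot be taken from the document. The 11 to 21 affected patients and the power of 0.86 and 0.64 rest on assumed rates. The conclusion rests only on the stated capture rule and on the unshown full protocol not extending it. The change is worth making because it is cheap and affects neither treatment nor assessor blinding, but it does not threaten the primary analysis.

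**What to change.** - In {11b} and {22}, add three items to the predefined events: falls, training-related injuries, and non-cardiac AEs that interrupt prehabilitation or postpone the cardiac procedure.
- Have the non-blinded investigator who already completes the t2 safety entry for both arms record them. The source should be one structured question, worded identically in both arms and covering randomization to t2.
- Include these events in the DSMB listing in {11b} and {21b}.
- In the same edit, reconcile {11b} (MACE, predefined SAEs) with {22} (all adverse cardiovascular events, all SAEs), so that one capture rule applies throughout.
- Report the between-arm comparison descriptively. State that intervention patients were supervised all day, that controls relied on recall, and that the question was asked unblinded.

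The cost is a few eCRF fields, one question at t2 and slightly more data entry. Some difference in ascertainment between the arms will remain.

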### Frequency and plans for auditing trial conduct {23}

An independent member of the Clinical Trials Unit of the University Medical Center Goettingen will act as a monitor and regularly review the recruitment centers. After a site initiation visit, the monitor will visit once a year the recruitment facilities and conduct an interim visit. The monitor will review documentation of AEs and SAEs, patient and study records. Prehabilitation centers will be monitored indirectly by reviewing medical records sent to recruitment centers after prehabilitation by monitor. During the first year of the intervention, prehabilitation centers will be visited by a consortium team member for follow-up as well as refresher training in the “Karl-Heinz” treatment manual.

### Plans for communicating important protocol amendments to relevant parties (e.g., trial participants, ethical committees) {25}

Any changes to the protocol that affect or could affect the study design or procedures, the objectives and hypotheses, or patient safety must be submitted as an amendment to the ethics committees of the study centers for consultation. The new version of the study protocol will be made available at the projects website, including the rationale for any changes. The clinical trial entry will be adjusted if necessary. Minor changes, such as organizational adjustments, changes in written manuals for the pure reason of clarification of any processes, or changes in responsibilities that have no effects on the defined study goals and conduction, will be agreed upon by the consortium management of PRECOVERY. In such cases, the ethical committee of the leading study center will be notified of such changes.

### Dissemination plans {31a}

The study report of the main outcomes will be submitted for publication to a peer-reviewed medical journal. Furthermore, a study report must be submitted to the Federal Joint Committee (G-BA). A summary report of the final study results will be disseminated to all project partners and on the project homepage. Authorship in scientific publications will adhere to the recommendations of the International Committee of Medical Journal Editors [68].

## Discussion

PRECOVERY is a randomized controlled multicenter trial with a calculated sample size of 422 participants that aims to examine the long-term efficacy (after 12 months) of a tailored prehabilitation for patients aged 75 years or older undergoing elective cardiac procedures. RCTs focusing on cardiac prehabilitation have shown positive effects in terms of delirium rate, QoL, length of stay in intensive care unit, and improved compliance of postoperative rehabilitation with good safety [69, 70]. Likewise, pre- and postoperative psychological interventions before cardiac surgery additionally led to significant reduction in length of hospital stay and increase in self-efficacy [71, 72]. In the last decade, five reviews with meta-analyses emphasizing on exercise-based prehabilitation prior to elective coronary procedure have been published [12–16] and have shown positive effects as well. In fact, multimodal intervention studies are rare. Mostly, only single-intervention modules were addressed in the context of prehabilitation. Two or three different modules have hardly been conducted. However, it is known from prehabilitation intervention studies with cancer patients that a multimodal prehabilitation approach should include at least physical activity training, nutritional counseling, and psychological support to be effective [73, 74]. In the field of cardiology/cardiac surgery, evidence-based conclusions are lacking—but parallels seem obvious.

The main cohort included in cardiac prehabilitation studies are patients prior to coronary artery bypass graft surgery and/or valvular surgery. To the best of our knowledge, there is currently no evidence proving the effect of a multimodal prehabilitation prior to cardiac intervention such as catheter-based valve reconstructions (e.g., MitraClip, TriClip).

PRÄP-GO [75] and PRECOVERY are the first multicentric prehabilitation trials in Germany focusing on the target to include prehabilitation before elective procedures in older patients into the German healthcare system.

Both studies are funded by the “Innovationsauschuss” [Innovation Committee] of the Federal Joint Committee (G-BA). The objective of PRÄP-GO is to evaluate the efficacy of a 3-week prehabilitation program for patients ≥ 70 years of age with frailty or pre-frailty undergoing different kinds of elective surgery. Primary endpoint is the care dependency 1 year after surgery [75]. In comparison, PRECOVERY focusses on patients prior to elective cardiac procedure and the efficacy of a 2-week prehabilitation program for patients ≥ 75 years of age. The co-primary outcomes are QoL and mortality 12 months after the cardiac procedure.

The PRECOVERY study design has several strengths. The multicenter alignment enables the establishment of structures that can be further used in the event of a positive evaluation of the new care form “Karl-Heinz.” Furthermore, the 12-month follow-up has the potential to identify long-term effects of prehabilitation prior to the cardiac procedure (e.g., mortality, QoL or cost-effectiveness). Finally, the study analyzes a broad and representative population in cardiac surgery and cardiology. However, this study has several limitations. Firstly, due to the type of the intervention, blinding of patients and various clinical staff is not possible. In PRECOVERY, only the assessment of outcomes is blinded. Secondly, complete standardization of the intervention is not feasible, as modules are selected according to the individual needs of the patients. To standardize the prehabilitation program “Karl-Heinz,” a treatment manual [see Additional file 3] was created in an expert workshop consisting of physicians, psychologists, sports scientists, and physiotherapists. The manual gives information about the intervention framework and how it can be customized to the individual needs of the participants.

In addition to the treatment manual, the exercise programs are based on current study recommendations in combination with recommendations from secondary prevention of treatment in cardiac patients.

This new form of care that aims in particular to further develop intersectoral care funded by the innovation fund of the Federal Joint Committee (G-BA), the highest decision-making body of the joint self-government of physicians, dentists, hospitals, and health insurance funds in Germany can be considered after positive evaluation to be directly incorporated in the German healthcare system in the long term.

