This intervention trial aims to fill the above described scientific gap. PRECOVERY (Prehabilitation “Karl-Heinz” focusing on cardiac and cognitive functions prior to the cardiac procedure: an analysis of the health status) will evaluate the clinical and health economic effectiveness of prehabilitation in older patients prior to an elective cardiac procedure in a multicenter, two-arm, outcome assessor-blinded randomized controlled trial, comparing the efficacy of a prehabilitation program with standard medical care (SMC). In Germany, SMC for these patients means that they remain at home until the planned cardiac procedure with general instructions (e.g., optimized medication plan) and the opportunity to contact their primary care physicians or cardiologists if they experience physical discomfort. After hospital discharge, all patients have the opportunity to participate in a 3-week in- or outpatient cardiac rehabilitation program that is integrated into the German healthcare system.

Patients will be followed up at intervals for a year after the cardiac procedure, in order to determine the effects of the prehabilitation intervention on 1-year mortality, QoL, and functional capacity, as well as other factors relating to clinical and health economic outcomes.

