### Trial design {8}

PRECOVERY is a confirmatory, randomized, controlled, two-arm parallel group, assessor-blinded multicenter intervention trial. If positive, we will confirm the efficacy of the multimodal prehabilitation intervention with regard to patients’ QoL, medical, cognitive, and psychosocial outcomes 12 months after an elective cardiac procedure. We will randomize 422 patients aged 75 years or older scheduled for an elective cardiac procedure to either (a) SMC (*n* = 211) or (b) a 2-week multimodal prehabilitation intervention (“Karl-Heinz”, *n* = 211) with an allocation ratio of 1:1 per hospital, patient’s age and gender with a follow-up period of 12 months. An additional component of the RCT is a detailed health economic analysis by the Department of Health Economics and Health Services Research, University Medical Center Hamburg-Eppendorf, Germany. Furthermore, an independent process evaluation in a mixed-methods design will be provided by the Department of General Practice of the University Medical Center Goettingen, Germany.

The primary aim is to demonstrate superiority of the intervention group compared to SMC group in terms of QoL and mortality 12 months after the cardiac procedure. The secondary aim is to show the superiority of the intervention group compared to the SMC group in terms of functional and cognitive capacity, heart-specific QoL, and activities of daily living after 12 months.

For the health economic analysis, we anticipate at least equivalence, a better non-inferiority in healthcare costs after 12 months in the intervention group compared to SMC group.

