### Intervention description {11a}

In contrast, the intervention group will receive a 2-week individualized prehabilitation program “Karl-Heinz” prior to the elective cardiac procedure. Study participation will have no influence on perioperative processes.

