### Provisions for post-trial care {30}

The study ends for all participants after the assessment t6 (follow-up 1 year after the cardiac procedure). All patients will sign the patient consent at the beginning of the study which includes the information that they agree to voluntarily participate in the clinical trial. The patient consent/information is available on request by the corresponding author. Participants carry no additional costs for post-trial care due to the fact that the German healthcare system does not require those who are insured to pay deductibles, co-payments, or out-of-pocket fees to receive medical care.

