### Outcomes {12}

The co-primary outcomes are the QoL and mortality after 12 months. The QoL is measured by the EuroQol questionnaire (EQ-5D-5L, [23]). The EQ-5D-5L consists of five dimensions (mobility, self-care, usual activities, pain/discomfort, and anxiety/depression) and is an instrument for measuring QoL and determining quality-adjusted life years in health economic studies [23, 24]. Each dimension is scored on a 5-point scale. The responses to the individual items are combined into a QoL index using established algorithms. In addition, patients rate their health status on a visual analog scale (EQ-VAS; range 0–100) [23].

The following secondary outcomes measures are defined:Activities of daily living (ADL) measured by Katz Index [25, 26]Physical performance rated by Short Physical Performance Battery (SPPB; [27])Cognitive performance measured by Montreal Cognitive Assessment Test (MoCa; [28, 29])Disease-specific QoL assessed by Heart Quality of Life Questionnaire (HeartQoL; [30])Anxiety and depression detected by Hospital Anxiety and Depression Scale (HADS; [31–33])Healthcare costs after 12 months. Healthcare resource utilization within 12 months after the cardiac procedure. During follow-up, all direct medical and non-medical healthcare-related resource utilization will be monitored using a validated questionnaire for health-related resource use by older patients (Fragebogen zur Inanspruchnahme medizinischer und nicht-medizinischer Versorgungsleistungen im Alter (FIMA; [34]) in combination with routine data transmitted by the AOK Lower Saxony and AOK Baden-Württemberg.

Further endpoints are as follows:

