### Recruitment {15}

The recruitment measures in PRECOVERY are integrated into the standard procedures of the participating recruiting centers. In these centers, patients scheduled for cardiac procedures in 4–6 weeks will be screened, informed, recruited (t0), and randomized (t1) according to the inclusion and exclusion criteria during a preoperative appointment in cardiology or cardiac surgery departments. To support the recruitment process, all referring centers will be informed about the study in advance and additional flyers will be produced to increase patient interest.

If the recruitment is not running well, the evaluation concept is designed through the use of the FIMA questionnaire in such a way that an extension to the inclusion of insured persons from other health insurance funds is also conceivable in Lower Saxony on the basis of the legal basis §630a German civil code.

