### Methods in analysis to handle protocol non-adherence and any statistical methods to handle missing data {20c}

Participants will be considered adherent to the intervention if they complete the minimal requirements (see Table 3). For participants to be included, they must have baseline values and at least one follow-up value, then the missing data will be imputed using multiple imputation. Details on the type of multiple imputation will be added following a blinded data review.

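### Co-primary mortality is timed from the cardiac procedure, not from randomisation, so as worded it has no value for randomised patients who never reach the procedure

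*Protocol article*

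**What the plan says.** All references are to the Protocol article.

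- **Endpoint timing.** Trial design {8} sets the primary aim as superiority "in terms of QoL and mortality 12 months after the cardiac procedure". The Discussion repeats it: "The co-primary outcomes are QoL and mortality 12 months after the cardiac procedure". Outcomes {12} gives no time origin: "The co-primary outcomes are the QoL and mortality after 12 months".
- **Follow-up clock.** The Background says "Patients will be followed up at intervals for a year after the cardiac procedure". Section {30} says "The study ends for all participants after the assessment t6 (follow-up 1 year after the cardiac procedure". Table 4 names t2 to t6 relative to the procedure and lists 1-year mortality only at t6.
- **Order of events.** Under Recruitment {15}, "patients scheduled for cardiac procedures in 4–6 weeks will be screened" and randomised at that preoperative appointment. Before the procedure, "the intervention group will receive a 2-week individualized prehabilitation program" (section {11a}).
- **Who is analysed.** Section {20c} says of participants to be included that "they must have baseline values and at least one follow-up value". Section {20a} names an intention-to-treat population, in its paragraph on the process evaluation.
- **What is collected before the procedure.** EQ-5D-5L is taken at t2. SAEs are documented from randomisation (section {22}). The DSMB reviews pre-procedure events in both arms (section {11b}).
- **Calendar.** Trial status ends recruitment at the end of October 2024 and follow-up at the end of October 2025.

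**The concern.** Reaching the procedure is a post-randomisation event that comes after the intervention and could be affected by it. An endpoint timed from that event has no defined value for a patient who dies while waiting or during prehabilitation, or whose procedure is cancelled. If an analyst follows the wording literally, mortality is compared among patients who survived to and received the procedure. That is not the comparison that randomisation protects. A death caused or prevented during the two weeks of treatment would then not count in a co-primary endpoint of a confirmatory trial.

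The follow-up-value rule adds to the problem. A patient who dies before t2 has a baseline but no later value, so the rule would drop that patient, and death itself would be the reason for leaving the analysis. That conflicts with intention-to-treat.

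**Working it through.** **1. The plan's own figure.** Inputs from section {14}: difference 0.045, SD 0.17, R-squared 0.25, two-sided 5%, power 80%, dropout 20%.

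- Adjusted SD = 0.17 × √(1 − 0.25) = 0.1472.
- n per group = 2 × (1.960 + 0.842)² × 0.1472² / 0.045² ≈ 168.02, rounded up to 169; total 338.
- With dropout: 338 / 0.8 = 422.5, stated as 422.

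The sample size reproduces and is not in dispute. It rests on EQ-5D-5L, and the time origin for mortality does not by itself change it.

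**2. What happens to each kind of patient under the wording.**

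| Patient | Mortality 12 months after the procedure | Rule in {20c} |
|---|---|---|
| Operated on | defined | included with any follow-up value |
| Dies after t2, before the procedure | undefined | included through the t2 value |
| Dies before t2 | undefined | not included |
| Procedure cancelled | undefined; t3 to t6 have no anchor date | depends on whether any follow-up value exists |

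**3. Share of time at risk before the procedure.** Planned gap 4–6 weeks (section {15}), then 52 weeks.

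- 4 / (4 + 52) = 7.1%; 6 / (6 + 52) = 10.3%.
- The 2-week intervention lies wholly inside this gap.

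**4. Which clock the dates fit.** A patient recruited on 31 October 2024 and operated on 4–6 weeks later has the procedure between 28 November and 12 December 2024. The t6 visit then falls between 28 November and 12 December 2025, after the stated end of follow-up. The dates fit 12 months from the last recruitment, not from the last procedure.

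**5. Possible size of the distortion (illustrative).** The article gives no pre-procedure death rate and no total mortality, so both are assumed. Let total mortality M from randomisation be equal in both arms, and let p be the proportion who die before the procedure. Counting only later deaths among operated patients gives (M − p) / (1 − p).

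| M | p, intervention vs control | Apparent mortality | Risk ratio |
|---|---|---|---|
| 12% | 2% vs 2% | 10.2% vs 10.2% | 1.00 |
| 12% | 2% vs 1% | 10.2% vs 11.1% | 0.92 |
| 12% | 3% vs 1% | 9.3% vs 11.1% | 0.84 |
| 12% | 5% vs 2% | 7.4% vs 10.2% | 0.72 |
| 12% | 1% vs 3% | 11.1% vs 9.3% | 1.20 |

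For M from 8% to 20% and the three splits with more pre-procedure deaths under intervention, the spurious risk ratio runs from 0.52 (M = 8%, 5% vs 2%) to 0.96 (M = 20%, 2% vs 1%).

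**6. How plausible those splits are.** At M = 12%, total deaths are 0.12 × 422 = 50.6. Spread evenly over time, 7.1–10.3% of them is about 4 to 5 pre-procedure deaths in both arms combined. The 2% vs 1% split is 4.2 + 2.1 = 6.3 deaths, slightly above that. The 3% vs 1% split (8.4 deaths) and the 5% vs 2% split (14.8 deaths) need a clearly higher hazard before the procedure than after it.

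**The case against.** A reader might infer that deaths before the procedure are left out of the primary comparison and that all follow-up starts at the procedure. The article does not support either statement.

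- No section says that earlier deaths are not counted. Mortality listed at t6 can be read as dead by t6, which would include them.
- Section {12}, the formal definition of outcomes, names no origin.
- Pre-procedure data exist: EQ-5D-5L at t2, SAEs from randomisation, and DSMB review of that period.
- The full protocol and the SAP are separate files that are not shown. The time origin of the joint model and the Kaplan–Meier curves may be fixed there, and its absence from the article is no fault.
- The follow-up-value rule stands next to multiple imputation and may be meant only for missing QoL values.
- Exclusion criteria such as NYHA IV, unstable angina and need for acute hospital treatment make a high pre-procedure death rate less likely. No rate is given, so any figure for missed deaths is an assumption.
- Measuring recovery QoL relative to the procedure is sensible.

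All of this limits the point but does not remove it. Trial design {8} and the Discussion do state a time point, and that time point follows the intervention. An SAP that starts the clock at randomisation would contradict them. The rule in {20c} carries no exception for deaths. Capturing a death as an SAE does not say whether it counts in the co-primary endpoint.

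**Conclusion.** The point holds in limited form. The co-primary mortality time point is worded from an event that follows both randomisation and the intervention. It is undefined for patients who die before the procedure or never have it. The inclusion rule in {20c}, read literally, drops deaths before t2 and so conflicts with the intention-to-treat population in {20a}. Section {12} names no clock, and the calendar dates fit a different one.

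That these deaths are actually excluded is not shown. Nor are the size and direction of any bias, which depend on pre-procedure death rates that the article does not report. With equal total mortality the bias is nil if those deaths are balanced. It favours the intervention if they are more frequent there, and it reverses if they are less frequent. At an assumed 12% total mortality, a 2% vs 1% split gives a risk ratio of 0.92; larger distortions need larger and less plausible imbalances. The 7–10% share of time at risk rests only on the planned 4–6 weeks.

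**What to change.** 1. Define co-primary mortality as all-cause death counted from randomisation, in all randomised patients as allocated, to a fixed and stated horizon. At the least, state that every death from randomisation through t6 counts. Keep 12 months after the procedure as a supportive analysis.
2. Start the survival clock of the joint model and the Kaplan–Meier curves at randomisation.
3. In {20c}, exempt deaths from the requirement of at least one follow-up value.
4. For patients not operated on, schedule the t4 to t6 assessments from the planned procedure date, and state how they enter both co-primary endpoints.
5. Align {8}, {12}, {20a}, {20c}, the Discussion and the Trial status dates with this definition.

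The cost is mainly wording, because SAEs are already recorded from randomisation, plus a few extra follow-up contacts. A fixed horizon from randomisation may differ slightly from the QoL visit at t6. The choice should be made before outcome data are seen, since picking the clock afterwards would weaken a confirmatory endpoint.
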